## Abstract

**Background:**

Mental health problems often lead to prolonged sick leave. In primary care, the usual approach towards these patients was the advice to take rest and not return to work before all complaints had disappeared. When complaints persist, these patients are often referred to psychologists from primary and specialized secondary care. As an alternative, ways have been sought to activate the Dutch occupational physician (OP) in primary care. Early 2000, the Dutch Association of Occupational Physicians (NVAB) published a guideline concerning the management by OPs of employees with mental health problems. The guideline received positive reactions from employees, employers and Dutch OPs. This manuscript describes the design of a study, which aims to assess the effects of the guideline, compared with usual care.

**Methods/Design:**

In a randomized controlled trial (RCT), subjects in the intervention group were treated according to the guideline. The control group received usual care, with minimal involvement of the OP and easy access to a psychologist. Subjects were recruited from two Dutch police departments. The primary outcomes of the study are return to work and treatment satisfaction by the employee, employer, and OP. A secondary outcome is cost-effectiveness of the intervention, compared with usual care. Furthermore, prognostic measures are taken into account as potential confounders. A process evaluation will be done by means of performance indicators, based on the guideline.

**Discussion:**

In this pragmatic trial, effectiveness instead of efficacy is studied. We will evaluate what is possible in real clinical practice, rather than under ideal circumstances. Many requirements for a high quality trial are being met. Results of this study will contribute to treatment options in occupational health practice for employees on sick leave due to mental health problems. Additionally, they may contribute to new and better-suited guidelines and stepped care. Results will become available during 2007.

**Trial registration:**

Current Controlled Trials ISRCTN34887348

## Background

### Common mental health problems and productivity loss

Common mental health problems can affect functioning to such an extent that they can lead to work absenteeism and presenteeism. These may result in productivity loss [1]. The prevalence of absenteeism due to mental health problems is reported to be between 10 and 18%, which causes extensive societal and financial costs [2-7]. Up to ninety percent of absenteeism is caused by minor, stress-related, mental health problems [3,4,6]. A small, but substantial part (over 20%) of these 'common' mental health problems result in long lasting productivity loss. In the Netherlands associated costs are enormous (9.407 billion Euros in 2004)[8,9].

### Stress management in Dutch occupational health care

For employees with common mental health problems, health care utilization is mainly restricted to primary care. In the Netherlands, primary care is regularly given by general practitioners  and occupational physicians (OPs). The majority of these OPs are working for commercially operating Occupational Health Services (OHSs). Each Dutch employee has to visit their OP for rehabilitation purposes when they are on sick leave. Therefore, the Dutch OP has a perfect opportunity to play a central role in the diagnosis and treatment of employees with common mental health problems. However, OPs often lack time and skills to deal with these employees [10,11]. Consequently, the approach of Dutch OPs towards employees on sick leave due to mental health problems has been minimal. The usual initial advice given by OPs and GPs towards these patients has been to take rest and only return to work when all complaints have disappeared. When complaints persist, these patients are often referred to psychologists from primary and specialized secondary care. Treatment by these psychologists is mostly symptom based rather than focusing on return to work. Most employees are not insured for these treatments. Recent Dutch, and Scandinavian, studies suggest that an inactive primary care that easily refers to specialized secondary care, may cause 'referral' delay in recovery [10-14]. In addition, referrals to specialized secondary care can be expensive for employees and employers, as they have to pay the price. As a consequence, patients may not get the optimal care they need.

### Stress management by occupational physicians

As an alternative to usual care, ways have been sought to activate the Dutch OP in primary care. As the OP is visited by each employee with or at risk of common mental health problems, the OP has a key role to detect them and influence their return to work. Therefore, a renewed position of the OP was introduced in a national evidence based guideline regarding the management by OPs of employees with mental health problems [15,16]. The guideline was published by the Dutch Association of Occupational Physicians (NVAB) in 2000. It promotes an active attitude and activating approach, instead of a minimal role of the OP. The guideline received positive reactions from employees, employers and Dutch OPs. However, there is reason to believe that the actual implementation of the guideline lags behind its acceptance, which questions the effectiveness of the guideline in practice [17,18].

### Study rationale/Objective

The aim of this study is to examine the effectiveness of the care by Dutch OPs according to the new common mental health guideline. The guideline may improve the effectiveness of occupational rehabilitation among workers with common mental health problems. This study will focus on the effects of training in the guideline on the skills of the OP, resulting in positive effects on return to work and treatment satisfaction.

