## Methods/Design

### Study design

In a randomized controlled trial (RCT) the effect of the 'Dutch national guideline on the management of employees with mental health problems by OPs' was evaluated. The focus of this study is to examine the new, more active role of Dutch OPs according to the new guideline. Therefore, subjects in the intervention group were treated by OPs, who were trained to provide treatment according to the guideline. The control group received usual care, with minimal involvement of the OP and if applicable, access to treatment by a psychologist.

The first hypothesis of this study is that the intervention will lead to health gain for employees on sick leave due to common mental health problems. This will result in faster recovery, less stagnation and less referrals to psychologists. Counseling, instead of symptom based treatment, will result in earlier return to work and consequently a decrease of productivity loss. The second hypothesis is that the intervention will additionally lead to relatively more treatment satisfaction of the employee, the employer and the OP. The third hypothesis is that a decrease of productivity loss and prevention of expensive referrals to secondary care, will reduce costs.

The recruitment of participants for the study started in January 2002 and ended in January 2005. There was a one year follow-up. The study was funded by the Dutch Ministry of Internal Affairs and Kingdom Relations, and the Insurance Agency on Medical Guidance of the Dutch Police (DGVP). The study design, protocol and procedures were approved by the Medical Ethics Review Committee of the VU University Medical Centre.

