OPs participating in the study received training in the guideline before the study started. During this training, consisting of a three-day course with 10–15 other OPs, knowledge about and practice in working with the guideline were educated and exchanged [21]. The course reflected the guideline by training OPs in multiple cognitive-behavioral prescriptive interventions, to stimulate the patients' acquisition of problem solving skills, and to structure the patients' daily activities. Information was given and OPs were trained to differentiate between adjustment disorder and depression, anxiety and other psychiatric disorders. Questionnaires were introduced, which can be helpful in making an accurate diagnosis. In addition, a graded activity treatment approach was introduced, which was based on a three stages model. This treatment approach resembles stress inoculation training, a highly effective form of cognitive behavioral treatment [16]. In the first stage, there is emphasis on information: understanding the origin and cause of the loss of control. Patients are also stimulated to do more non-demanding daily activities. In the second stage, patients are asked to draw up an inventory of stressors and to develop problem solving strategies for the causes of stress. In the third stage, patients put these problem solving strategies into practice and extend their activities to include more demanding ones. The patients' own responsibility and active role in the recovery process was emphasized and the same goes for the importance of an early start of the intervention aimed at the acquisition of coping skills and at regaining control. Problem solving activities according to a time contingent scheme were educated and practiced. The OPs were free to choose the specific tools for use in each phase of the process. The training course was given by four persons: an experienced OP/psychologist, a psychologist/therapist, an experienced general practitioner/researcher on emotional distress, and a psychiatrist.

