#### Contamination

As randomization was done on patient level, OPs which were trained in the guideline treated all participants. Obviously this situation created a risk of treatment contamination between the groups. The trained OP treated an employee in the intervention group according to the guideline, as far as this happens in practice. The same OP treated an employee in the control group with minimal involvement and if applicable, direct referral to a psychologist. A cross-over learning effect may have happened in the control group, since the OP can adhere to the guideline in this group as well. The other way around, the OP may have referred an employee in the intervention group to a psychologist as well. The guideline promotes this in case of stagnation in recovery or in case of severe mental health problems of the employee. However, we tried to maximize the contrast by creating a situation in which referral to the psychologist in the control group was always granted by the insurance company (DGVP).

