#### Guideline adherence by the OP

The aim of this study is to examine the effectiveness of the management by Dutch OPs, under the expectation that (training in) the guideline will lead to additional skills for the OP and consequently to positive outcomes. To explore our hypothesis that the guideline leads to additional skills and outcomes, we examined the performance by the OP according to the guideline (guideline adherence). Guideline adherence by the OP was checked by means of an audit of the medical files. Guideline adherence was defined as the total score on ten validated performance indicators for the treatment of each participant by the OP (table 5)[11,18,36]. For each performance indicator, we used validated criteria. If a criterion was not met, the case was assigned 1 for that performance indicator. If all applicable criteria for a performance indicator were met, the resulting score was 0 for that case. The medical files of all the participants were assessed on if they met the criteria of the different indicators (0=adequate care; 1=deviant care). In this way an average performance rate was obtained for each performance indicator. Furthermore, a total score of all performance indicators was calculated (guideline adherence). Guideline adherence was dichotomized into adequate adherence and deviant adherence. Adherence was considered deviant if three or more performance indicators were assigned a score of 1, and adequate if less than three performance indicators had a score of 1.

**Table 5 T5:** Performance indicators guideline adherence and their criteria 1 = deviant care, NA = Not applicable

**PI 1**	**Assessment of symptoms**	**Score**
Criteria:	1. Presence or absence of essential symptoms of anxiety disorder and depressive disorder should be noted in file	
	2. Presence or absence of distress symptoms (fatigue, concentration problems, sleeping problems, and emotional reactivity) should be noted in file	
	*One or both criteria not met within 2 consultations?*	PI1 = 1

**PI 2**	**Correct diagnosis**	

Criteria:	1. Diagnosis should be noted in file	
	2. Diagnosis should be correct:	
	- IF adjustment disorder: at least one psychological distress symptom should be noted in file	
	- IF depressive disorder: at least one essential symptom AND five depressive symptoms should be noted in file	
	- IF anxiety disorder: at least one anxiety disorder should be noted in file	
	3. Diagnosis should not be missed if criteria above apply	

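### The stated focus on the effect of guideline training cannot be estimated, because the same trained OPs treat both arms; the main aim, guideline care versus usual care, is not affected

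*Protocol article*

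**What the plan says.** The protocol article states its purpose in several places, and they do not all match.

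- *Study rationale/Objective* opens with an aim about care: "The aim of this study is to examine the effectiveness of the care by Dutch OPs according to the new common mental health guideline". Two sentences later it gives a focus on training: "This study will focus on the effects of training in the guideline on the skills of the OP", with effects on return to work and treatment satisfaction expected to follow.
- *Study design* gives a different focus: "The focus of this study is to examine the new, more active role of Dutch OPs according to the new guideline". Its three hypotheses concern the intervention and do not mention training. The same section describes the intervention arm this way: "subjects in the intervention group were treated by OPs, who were trained to provide treatment according to the guideline". It says nothing there about the training of the OPs who see control patients.
- *Intervention* settles the timing: "OPs participating in the study received training in the guideline before the study started".
- *Contamination* settles who treats whom: "OPs which were trained in the guideline treated all participants". It adds that a control patient is managed by the same OP, with little involvement and referral to a psychologist where applicable.
- *Guideline adherence by the OP* returns to the skills route. It expects the guideline, with training in it named in parentheses, to add to OP skills and so improve outcomes, and continues: "To explore our hypothesis that the guideline leads to additional skills and outcomes, we examined the performance by the OP according to the guideline". The tool is an audit of participants' medical files in both arms.
- *Contamination between study groups*, in the Discussion, confirms that randomisation was at patient level because there were few OPs.

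**The concern.** A trial can estimate the effect of a factor from its randomised comparison only if that factor differs between the arms. Here training does not differ. The documents describe no untrained OPs and no measurement of the same OPs before the course.

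What is at stake is interpretation. The Background says that OPs often lack the skills for these employees and that implementation of the guideline lags behind its acceptance, so readers will look to this trial for evidence on training.

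- A null result on return to work could be read as showing that training does not help, although trained skills may have reached both arms.
- A positive result could be credited to training that both arms shared.
- Similar adherence in the two arms could mean that training changed nothing, or that it changed care for every patient.

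The wording under *Study design* makes these misreadings easier, because it mentions trained OPs only for the intervention arm.

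**Working it through.** There is no figure in the plan to reproduce; the question is what the design can identify.

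**Inputs**

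- Training, T: equal to 1 for every participating OP (*Intervention*; *Contamination*).
- Allocation, Z: 1 for guideline care and 0 for usual care, randomised by patient (*Randomisation*; *Contamination between study groups*).
- Comparators for training: none described, either untrained OPs or files from before the course (*Guideline adherence by the OP*; *Data collection*).

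**Contrast**

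Write the mean of any outcome (adherence, satisfaction, time to return to work) as

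Y = b0 + bT·T + bZ·Z + bTZ·T·Z.

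With T = 1 throughout:

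- intervention arm: b0 + bT + bZ + bTZ
- control arm: b0 + bT
- difference between arms: bZ + bTZ

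The effect of training is bT in patients managed as usual care and bT + bTZ in patients managed by the guideline. The trial observes two arm means, and the model has four unknowns. The term bT has gone from the difference, and bTZ appears only in a sum with bZ.

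**Illustration** (arbitrary units, chosen only to show the algebra)

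| bT | bZ | bTZ | Difference seen, bZ + bTZ | Training effect in guideline patients, bT + bTZ |
|---|---|---|---|---|
| −10 | −5 | 0 | −5 | −10 |
| −30 | −5 | 0 | −5 | −30 |
| 0 | −5 | −10 | −15 | −10 |

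Rows 1 and 2 show the same difference between arms with different training effects. Rows 1 and 3 have the same training effect in guideline patients with different differences. The observed contrast therefore does not determine the training effect in either direction.

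**Does the audit fill the gap?**

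No. It scores files of trial participants, so T = 1 there too and the same algebra applies to adherence. Its compliance rule confirms its purpose: care counts as compliant in the intervention arm when adherence is adequate, and in the control arm when adherence is deviant. A trained OP who applies the new skills to a control patient is counted as non-compliant. The audit thus measures contrast in care and contamination, not a gain in skill.

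**Does the process evaluation fill it?**

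No. Relating each performance indicator to the outcomes, as *Data analysis* plans, gives an association among patients of trained OPs. It does not show what those OPs would have done untrained.

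**The case against.** The strongest reply is that one loose sentence is being treated as the objective. Much of this stands. The aim that opens *Study rationale/Objective*, the Abstract, the three hypotheses and the definition of the intervention all concern guideline care against usual care, which is what is randomised. Training is not listed as an outcome and has no analysis of its own. Under *Guideline adherence by the OP*, training appears only in parentheses and as an expectation. The article also discloses that the same trained OP treats both arms and that learning may carry over to controls, and it says that randomising physicians as well as patients would have been best.

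This limits the point but does not remove it. The disclosure concerns contamination of care between arms. No section says that the effect of training cannot be estimated, and none withdraws the focus sentence.

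Three stronger readings are tempting, and the documents do not support them.

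- A reader might infer that every effect of training cancels. That is exact only for the part common to both arms. A part expressed only under the instruction to follow the guideline (bTZ) remains in the contrast, inseparable from allocation.
- A reader might infer that the trial cannot answer its main question. It can: the main aim does not require training to vary.
- A reader might infer that the authors plan to report that training works or fails. No section plans such a conclusion; the risk lies in how the stated focus will be read.

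**Conclusion.** The point holds, confined to the focus sentence under *Study rationale/Objective* and its repeat under *Guideline adherence by the OP*. Both name an effect of training that this design does not identify, and the audit of participants' files does not supply it. The randomised comparison estimates the effect of instructing trained OPs to manage a patient by the guideline rather than by usual care.

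No numerical size can be given: the documents contain nothing on OP performance before training or on how far skills carry over to control patients. The consequence is for what may be claimed, not for the main aim, the hypotheses, the outcomes, the sample size or the planned comparison of arms.

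The conclusion assumes that the article's account is complete on two facts: that no untrained OP treated participants, which it states in substance, and that no assessment before training exists, since none is described.

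**What to change.** 1. Under *Study rationale/Objective* and *Guideline adherence by the OP*, replace the training statements with the randomised contrast: trained OPs instructed to manage a patient by the guideline, against the same OPs instructed to keep their involvement minimal, with a psychologist available.
2. Under *Study design*, make clear that the same trained OPs serve both arms.
3. State the permitted conclusion: neither a null nor a positive result, nor the comparison of adherence between arms, estimates the effect of training. Describe the audit as a measure of contrast in care and of contamination.

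The cost is rewording only. Analysis and reporting are described as still to come, so the permitted conclusion can still be set. The downside is that the training claim is given up.

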## Methods/Design

### Study design

In a randomized controlled trial (RCT) the effect of the 'Dutch national guideline on the management of employees with mental health problems by OPs' was evaluated. The focus of this study is to examine the new, more active role of Dutch OPs according to the new guideline. Therefore, subjects in the intervention group were treated by OPs, who were trained to provide treatment according to the guideline. The control group received usual care, with minimal involvement of the OP and if applicable, access to treatment by a psychologist.

The first hypothesis of this study is that the intervention will lead to health gain for employees on sick leave due to common mental health problems. This will result in faster recovery, less stagnation and less referrals to psychologists. Counseling, instead of symptom based treatment, will result in earlier return to work and consequently a decrease of productivity loss. The second hypothesis is that the intervention will additionally lead to relatively more treatment satisfaction of the employee, the employer and the OP. The third hypothesis is that a decrease of productivity loss and prevention of expensive referrals to secondary care, will reduce costs.

The recruitment of participants for the study started in January 2002 and ended in January 2005. There was a one year follow-up. The study was funded by the Dutch Ministry of Internal Affairs and Kingdom Relations, and the Insurance Agency on Medical Guidance of the Dutch Police (DGVP). The study design, protocol and procedures were approved by the Medical Ethics Review Committee of the VU University Medical Centre.

### Participants

#### Setting

This study was conducted with the cooperation of the Dutch police force, which is an organization with a relatively high incidence of mental health problems. These problems are mainly work related as police work has inevitable risks and stress may develop as 'part of the job' [19]. The employer of the Dutch police, the Ministry of Internal Affairs, tried to provide an optimal care and was open to alternative effective treatments. Each Dutch police employee was insured by the insurance company, the DGVP. DGVP tried to provide optimal usual care by partly financing referrals by OPs of police employees with mental health problems to a commercial psychotherapeutic centre as part of a protocol. Therefore, these police departments and their occupational health care provided a representative study population.

This intervention was developed for the occupational health care setting with its typical case load of common mental disorders. Two police departments were chosen because they had contracts with the same private OHS, i.e. Commit. Consequently, uniformity in treatment was more secured. Commit is one of the largest OHSs in the country. The police departments, i.e. Zaanstreek-Waterland and Hollands Midden, were located in the South-West of the Netherlands. Hollands Midden comprises approximately 1700 employees; Zaanstreek-Waterland approximately 800, totalling a source population of 2500 police employees.

Because we wanted to prevent employees with chronic disability to participate in the study, each employee on sick leave due to mental health problems before the start of the study in 2002, was detected by the OHS. They received a treatment by a psychologist in secondary care funded by the DGVP.

